#### SMC Plus GES

In addition to receiving SMC, participants in the GES arm will be given a copy of a self-help booklet describing a 6-step program of graded exercise that should take approximately 12 weeks to complete. A physiotherapist will then join the participant for a 30-minute appointment either face-to-face in the clinic or via telephone/Skype™ within 5 working days of randomization. The physiotherapist will explain how the booklet should be used, explain steps 1 to 4 of the booklet, and answer any questions/concerns of participants. The physiotherapist will provide up to 3 further 20-minute telephone or Skype™ support appointments over the next 8 weeks. These 3 follow-up appointments will take place approximately 1 to 2, 4 to 5, and 7 to 8 weeks after the participant’s initial appointment. The physiotherapists will be trained and experienced in delivering GET as a treatment for CFS/ME, and in how to guide and support participants in their use of the booklet without providing additional therapy. The emphasis of guidance/support will be on solutions provided by the booklet and how to apply what is learned, and will follow a support guidance checklist. Contacts with the physiotherapist will be audio-recorded, with informed consent, for training and supervision purposes to ensure that therapists adhere to the guided self-help manual. The GES supervisor will listen to a random sample of the recordings throughout to ensure therapists are maintaining a consistent approach.

*The Guided graded Exercise Self-help (GES) booklet* is based on the approach of GET developed for the PACE trial [11], which was itself based on effective approaches tested in previous trials [9]. GES is also based upon the recommendations made by NICE in 2007 [7]. Patients with CFS/ME attending clinics at St Bartholomew’s and King’s College hospitals in London piloted the booklet. Engaging and encouraging participants to undertake their exercise plans using the GES booklet are cornerstones of the guidance and will be its main focus.

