#### Safety Measures and Reporting

For safety outcomes, we will include serious adverse events (SAEs), serious adverse reactions to trial treatments (SARs), and serious deteriorations (SDs). SAEs will be defined according to usual clinical trial definitions (ie, an event that is fatal, life-threatening, or results in or prolongs hospitalization; an increase in severe and persistent disability or incapacity; self-harm; or any other important condition that may require medical or surgical intervention to prevent the above [10] and will be reported to the appropriate authorities in the standard manner. SARs are SAEs that are considered to be a reaction to any trial therapy or drug prescribed. SDs will be defined as any of the following outcomes: CGI scores of 6 and 7, active withdrawal from the intervention due to worsening, or a reduction on the SF-36 PF scale by 10 or more points. Participants will record any nonserious adverse events (NSAEs) in their follow-up questionnaire. An adverse event is defined as any clinical change, disease, or disorder recorded by the participant, whether or not it is considered to be related to the trial or its treatments. Participants will be asked to record whether they believe the adverse event was “related to following the GET guide.” In the event of an adverse event (AE), the center leader will judge the seriousness of the event, and, if judged to be serious, the relationship to a trial supplementary therapy or SMC prescribed treatment, and the expectedness of the event. The trial manager will report all SAEs to the principal investigator (PI) within 24 hours, regardless of the relationship to trial treatment. Reporting of SAEs and SARs will be carried out according to normal regulatory research governance requirements.

After an SAE or SAR, the center leader will make a decision as to whether the participant should be withdrawn from either randomized treatment or from the trial, or if an alteration in their SMC is needed; arrangements will be made for further assessment and management as required. The trial manager will provide the center leader with monthly follow-up reports until resolution. These reports will be communicated to the Data Monitoring and Ethics Committee (DMEC), and other appropriate authorities via the trial manager.

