#### Non-Responders

If a returned form is incomplete, the researcher will contact the patient, usually by telephone, to acquire any missing data. In the event that no outcome data is completed or returned after 2 telephone attempts spaced 1 week apart, the researcher will email or text the participant to ask for answers over the telephone or via email solely for the 2 primary outcomes and the CGI. The researcher will make a file note that the outcome data were collected in this way. If a participant withdraws from the treatment, but not the trial, data will be collected in the usual way. If the participant is not willing to provide all follow-up data, a request will be made to complete only the primary outcome and CGI; if the participant agrees, these will be completed immediately.

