#### Sensitivity Analysis

Sensitivity analysis will be conducted to assess the impact of missing data on our results. We will estimate whole-scale missing data due to loss to follow-up using multiple imputation by chained equation. This will allow us to conduct a strict ITT for all respondents who took part at baseline. Following recent guidelines, we will also conduct a sensitivity analysis that will take into account the partially nested design of the study and, therefore, assess the potential impact of the “therapist effect” on our results [46]. Further analysis will be conducted to adjust for potential confounders, including sex and age.

A per-protocol analysis will serve as a further sensitivity analysis to investigate the robustness of the conclusions of the primary analysis, following departures from the randomized intervention policies. This will exclude those participants in the control arm who used a GET self-help approach. Subgroup analyses including only those meeting the Oxford or CDC criteria for CFS will also be undertaken. We will analyze moderators of improvement, such as these criteria, but also depression and severity of physical function and fatigue. These subgroup analyses are exploratory and will be interpreted with due caution [47].

#### Analysis for Hypotheses 2 and 3

Chi square will be used to describe any difference in satisfaction (ie, satisfied vs nonsatisfied) across treatment arms and any differences in SAEs, SARs, or serious deterioration (1+ vs none) across treatment arms.

The above plan is what we intend to do; however, the final analyses reported may differ from those planned, allowing for *post hoc* analysis where it is indicated [48]. We will report alternative methods if statistical models do not converge, and omit planned analyses that are superseded, redundant, or no longer of interest. We will report any changes in consequent papers.

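### The minimum follow-up requests contain no adverse event question, so non-serious and possibly serious event counts will be incomplete for participants reached only that way

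*Protocol article*

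**What the plan says.** The Non-Responders section of the protocol article describes two short requests. If no outcome data arrive after two telephone attempts a week apart, the researcher emails or texts to obtain answers "solely for the 2 primary outcomes and the CGI". The second is for reluctant participants: "If the participant is not willing to provide all follow-up data, a request will be made to complete only the primary outcome and CGI". The default for people who stop treatment but stay in the trial is full collection: "If a participant withdraws from the treatment, but not the trial, data will be collected in the usual way".

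Safety Measures and Reporting gives the route for non-serious events: "Participants will record any nonserious adverse events (NSAEs) in their follow-up questionnaire". It defines an adverse event as "any clinical change, disease, or disorder recorded by the participant". Grading follows: "In the event of an adverse event (AE), the center leader will judge the seriousness of the event". The trial manager then passes SAEs to the principal investigator within 24 hours.

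Analysis for Hypotheses 2 and 3 plans a chi-square test for "any differences in SAEs, SARs, or serious deterioration (1+ vs none) across treatment arms".

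**The concern.** The short requests name their content exhaustively, and no item asks about an adverse event. The omission is therefore a stated restriction, not detail lost in condensing the protocol into an article. For anyone who answers only the short set, the one described route for non-serious events is closed.

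The gap may extend to serious events. The center leader can grade only what has come to light, and the 24-hour line carries SAEs that are already known. An admission known only to the participant could go unrecorded. The full 12-week questionnaire has two other items that might have revealed it: the service-use inventory (CSRI) and the question on new health problems. The short set drops both.

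At stake is the completeness of the safety data behind the third hypothesis. The Discussion makes release of the booklet conditional on the trial showing it to be safe, among other things.

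**Working it through.** **Step 1. Which safety outcomes does the short set cover?**

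| Safety outcome | How the article says it becomes known | Covered by the short set? |
|---|---|---|
| Non-serious adverse events | Participant records them in the follow-up questionnaire | No |
| SAEs and SARs | Center leader judges a known event; trial manager reports it. No systematic detection route is described | Not asked; depends on another source |
| Serious deterioration: CGI 6-7 | Self-rated CGI | Yes |
| Serious deterioration: SF-36 PF fall of 10 or more | SF-36 PF | Yes |
| Serious deterioration: active withdrawal due to worsening | Withdrawals recorded (Departure from Intended Treatment) | Recorded separately |

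The gap therefore lies in the first two rows.

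**Step 2. Is there a later catch-up?** The 12-month list is CFQ, SF-36 PF, CGI, EQ-5D and CSRI. It names no adverse event item. The CSRI might show an admission indirectly.

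**Step 3. The plan's own figure.** The article gives no figure on this point. The only input taken from it is the total of 218. That total reproduces: for 8 points, SD 18, two-sided alpha 2.5% (sidedness assumed) and 80% power, the normal approximation gives 97 per group and the t-test version 97.5, so 98. Then 98 / 0.90 = 108.9, so 109 per group and 218 in total. The planned 10% loss to follow-up is not the share on the short route, because participants on that route do supply primary outcomes.

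**Step 4. SAEs that might go unasked.** Assumptions: a share f of 5-15% on the short route, and an SAE risk r of 2-5%, the same as in everyone else.

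- Participants on the short route: 218 × 0.05 = 10.9 to 218 × 0.15 = 32.7.
- With an unasked SAE (218 × f × r): 218 × 0.05 × 0.02 = 0.2 to 218 × 0.15 × 0.05 = 1.6.
- Whole-trial total at the same risk: 218 × 0.02 = 4.4 to 218 × 0.05 = 10.9.

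With equal risk in both groups, the unasked fraction of all SAEs is simply f, 5-15%. It is an upper limit on what is missed, since some events would surface by another route.

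**Step 5. Non-serious events, GES arm only (109).** Assumptions: 10% on the short route, 20% of full responders reporting an event, and a rate 1 to 3 times that on the short route.

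- Unrecorded: 109 × 0.10 × 0.20 × (1 to 3) = 2.2 to 6.5 participants.
- True proportion: 0.90 × 0.20 + 0.10 × 0.20 × (1 to 3) = 20% to 24%.
- Observed among full responders: 20%. If a missing report were counted as no event: 0.90 × 0.20 = 18%.

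**The case against.** The strongest reply is that a short minimum set is a sensible way to limit burden, and that this one already carries harm measures. The article says that the CGI serves safety as well as efficacy. This stands: with the SF-36 PF and the recorded withdrawals, the serious deterioration composite survives almost intact. It does not fill the gap, because SAEs and SARs are listed as separate outcomes. Neither scale can identify a hospitalization or its relation to treatment.

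Second, only non-serious events are expressly tied to the questionnaire. A reader might infer that SAEs are collected solely that way; the article does not say so, and a fuller protocol, not shown, may describe how they are detected. This stands as well, so under-ascertainment of SAEs is a possibility only.

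Third, a reader might infer that the people most likely to have been harmed are never asked about harm. The text does not support that. Participants who leave treatment are first followed up in full, non-responders have already been mailed the whole questionnaire and telephoned twice, and no passage says that people on the short route fared worse.

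Fourth, a reader might take the at-least-one-versus-none test to mean that unasked participants are counted as having no event. The article does not say how they are classed, and that detail may be left to an analysis plan.

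Fifth, the arms differ in contact. After an initial appointment, GES participants have further sessions: "The physiotherapist will provide up to 3 further 20-minute telephone or Skype™ support appointments over the next 8 weeks". No scheduled trial contact before week 12 is described for the control arm. But the Non-Responders rule does not cause this difference. Taken alone, extra detection under GES would count against GES. What remains is that the short request is a point where both arms could be asked the same question, and it is not asked.

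**Conclusion.** The point holds in limited form. Non-serious event counts will be incomplete for participants followed up only by the short requests. SAE and SAR counts for the third hypothesis may be incomplete for them too. Serious deterioration is largely protected.

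The size rests wholly on assumed inputs: about 0.2 to 1.6 participants with an SAE unasked, if 5-15% use the short route at a 2-5% risk. A reader might assume a much higher risk among these participants. At 5-20%, the same arithmetic gives 218 × 0.05 × 0.05 = 0.5 to 218 × 0.15 × 0.20 = 6.5. Nothing in the article supports such rates, and the upper value exceeds the whole-trial total of 4.4 at an overall risk of 2%. Nor do the documents support a claim that the between-arm SAE comparison is biased by a known amount or in a known direction. Still, where only a handful of SAEs is expected, one or two missed could matter, and the remedy is cheap.

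**What to change.** In Non-Responders, add one brief question to both short requests: whether any serious event (for example a hospitalization) or other adverse event has occurred since randomization.

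In the safety analysis, keep every known SAE from any source in the main between-arm comparison, and report by arm how many participants had adverse events ascertained. A comparison limited to events from the common 12-week question may be shown only as a supplement. As the main analysis it would remove known SAEs, including those of people who were hospitalized and did not reply.

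The cost is a slightly longer minimum contact and one added line in the safety table. The article reports that follow-up is complete, so for this trial the usable part is the analysis and reporting. The file notes that the researcher makes when outcomes are obtained by the non-responder route should identify many of the participants concerned.

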#### 12-Months Post-randomization

The primary purpose of the 12-month follow-up will be to obtain the health-economic assessment (see section below); however, we will also collect data on the primary outcome measures and the CGI so that we can assess longer-term physical functioning, fatigue, and change in overall health and CFS. The following information will be collected via questionnaires sent in the mail with a stamped addressed envelope for return: CFQ, SF-36 PF, CGI, EQ-5D, and CSRI.

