#### Economic Evaluation

The economic analysis will take a health and social care perspective. Service use will be combined with appropriate unit costs (eg, from Kent University and NHS Reference Costs) to generate service costs. QALYs gained over the period from baseline to 12-week follow-up will be generated using area-under-the-curve methods from the EQ-5D (using published tariffs from the University of York) combined with costs in the cost-effectiveness analysis. If the intervention group has lower costs and better outcomes than the control group, then the intervention will be seen as “dominant.” If the intervention group has higher costs and better outcomes, we will use incremental cost-effectiveness ratios to identify the extra cost incurred to achieve one extra QALY. Uncertainty around cost-effectiveness estimates will be explored using cost-effectiveness planes (produced from outcome-cost combinations from 1000 bootstrapped resamples). Interpretation will be aided using cost-effectiveness acceptability curves derived using the net-benefit approach with values between £0 and £100,000, placed on a QALY gain so as to include the threshold used by NICE (2007) [7]. We will also conduct similar analyses using costs and the primary outcome measure. However, QALYs are the main measure for the economic evaluation given that thresholds for cost-effectiveness used by NICE exist.

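### The reduced data set for non-responders and for those unwilling to give full follow-up omits EQ-5D and CSRI, with no exception at 12 months, where the economic assessment is the main purpose

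*Protocol article*

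**What the plan says.** The Non-Responders section of the protocol article describes four situations.

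- **Form returned but incomplete:** "If a returned form is incomplete, the researcher will contact the patient, usually by telephone, to acquire any missing data". No instrument is left out.
- **Treatment stopped, participant still in the trial:** "If a participant withdraws from the treatment, but not the trial, data will be collected in the usual way".
- **Nothing returned after two telephone attempts a week apart:** the researcher emails or texts to seek replies by telephone or email, "solely for the 2 primary outcomes and the CGI".
- **Participant unwilling to give all follow-up data:** "a request will be made to complete only the primary outcome and CGI". The singular is read here as both current primary outcomes.

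The section names no time point. On the economic side, the 12-Months Post-randomization section states: "The primary purpose of the 12-month follow-up will be to obtain the health-economic assessment". The instruments listed there are "CFQ, SF-36 PF, CGI, EQ-5D, and CSRI", with the clinical scales introduced as an addition. The Economic Evaluation section states that "QALYs are the main measure for the economic evaluation" and derives QALYs from EQ-5D by area under the curve between baseline and 12 weeks. The section on 12-week follow-up under the economic analysis counts QALYs among the main outcomes.

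**The concern.** The two reduced sets keep SF-36 PF, CFQ and CGI and drop EQ-5D and CSRI. At 12 weeks that protects the primary outcomes, but it loses the only follow-up value that enters the QALY. At 12 months the order of priority is the reverse of the stated purpose: the additional measures are kept, and those the contact mainly exists to obtain are not requested.

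The efficacy and economic results may then describe differently selected groups. The primary analysis takes everyone with follow-up information, which includes people reached by the reduced request. A complete-case QALY analysis would leave them out. The planned analysis of costs against the primary outcome is also affected, because these people supply the outcome but not the CSRI part of the cost. Cost-effectiveness matters to the conclusions: the Discussion links a possible recommendation to commissioners to it.

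**Working it through.** **1. Which data survive for a person reached only by the reduced request**

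| Item | Source in the article | Available? |
|---|---|---|
| SF-36 PF, CFQ, CGI | Reduced request | Yes |
| Follow-up EQ-5D, hence observed QALY | Questionnaire | No |
| Primary and secondary care, medication, outside therapy, informal care | CSRI | No |
| Number and length of GES contacts | Physiotherapist record | Yes |
| Therapy sessions to one year | Clinic notes and databases | Yes |

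The last three rows come from the section on measures for the economic evaluation. The gap is real but confined to EQ-5D and CSRI-reported use.

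**2. The plan's own sample size**

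Inputs from the Sample Size section: difference 8, SD 18, alpha 2.5% (taken as two-sided), power 80%, loss about 10%. The two-sample t-test calculation gives 97.5, so 98 per group. Then 98 / 0.9 = 108.9, so 109 per group and 218 in total. For CFQ (difference 3, SD 6) it gives 77.3, so 78; 78 / 0.9 = 86.7, so 87 per group and 174 in total. Both stated totals reproduce.

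**3. Precision of a complete-case economic analysis**

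The article gives no share for the reduced route, so the total share without economic data, m, is an assumption. Remaining number = 218 × (1 − m). Interval width relative to the planned 10% loss = √(0.9 / (1 − m)).

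| m | Remaining | Relative width |
|---|---|---|
| 10% | 196 | 1.00 |
| 15% | 185 | 1.03 |
| 20% | 174 | 1.06 |
| 25% | 164 | 1.10 |
| 30% | 153 | 1.13 |

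If 10% have no primary outcome either, the efficacy analysis keeps about 196 in every row. The gap between 196 and the second column is then the number who count in one analysis and not in the other.

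**4. Possible bias in the 12-week QALY difference**

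Under area under the curve with two time points, the 12-week EQ-5D carries a weight of 0.5 × 12/52 = 0.115. Let a share f of an arm lack EQ-5D, with a true mean lower by d than that of the arm's responders. Then

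bias = 0.115 × (f·d in GES − f·d in SMC).

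Neither f nor d is in the article. With assumed values in one arm only:

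- f = 0.05, d = 0.05: 0.0003 QALY
- f = 0.10, d = 0.10: 0.0012 QALY
- f = 0.15, d = 0.15: 0.0026 QALY

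The sign is positive if the gap is in GES, negative if it is in SMC, and the bias is zero if f·d is equal in both arms. This shows how the mechanism works. It does not estimate the bias.

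**The case against.** The reduced set is a last resort. It starts only after two telephone attempts, or after someone has declined full follow-up. A short request protects the primary outcomes, which is a legitimate trade-off at 12 weeks. That stands, and it is why EQ-5D should come after the primary outcomes there. It does not justify the same order at 12 months.

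A reader might infer more than the documents support:

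- **That QALYs and costs rest only on people who returned full questionnaires.** They do not. Incomplete forms are chased for everything, people who stop treatment but stay in the trial are followed as usual, and GES contacts and later therapy come from records.
- **That a 12-month QALY result is biased.** The article specifies QALYs only to 12 weeks. For 12 months it describes a costing of doctor and therapist appointments.
- **That missing economic data are left unhandled.** The Sensitivity Analysis section plans chained-equation imputation of whole-scale missing data due to loss to follow-up. It does not name EQ-5D or CSRI, but it does not exclude them, and such detail commonly sits in a full protocol or analysis plan that is not shown.
- **That the QALY gain is overstated.** This needs reluctant responders to be doing worse in the GES arm in particular. The article says nothing on that.

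**Conclusion.** The point holds in a limited form. As written, the rule loses observed EQ-5D and CSRI-reported service use from people who are reached and who count in the efficacy analysis. At 12 months it conflicts with the stated purpose of the contact. The efficacy analysis itself is unaffected.

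The size is unknown, because the article does not say how many people were followed only by the reduced request. The 3% to 13% wider intervals rest on assumed shares of 15% to 30% without economic data, and on a complete-case analysis. The QALY bias figures rest wholly on assumed inputs and can take either sign. This is a low-cost improvement to a stated rule, and it does not show that the economic result is wrong.

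**What to change.** **Collection rule (Non-Responders section).** Add EQ-5D to both reduced sets. At 12 weeks, ask it after the primary outcomes so that these are not put at risk. At 12 months, ask it first, followed by a brief service-use question. The cost is a few short questions and slightly more burden on reluctant responders.

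**Analysis, since collection is closed.** The article reports that long-term follow-up ended in March 2016, so only analytic steps remain.

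- Apply the chained-equation imputation already planned under Sensitivity Analysis to EQ-5D and CSRI costs for all randomised participants.
- Use the SF-36 PF, CFQ and CGI collected by the reduced request as predictors, and enter the record-based GES contacts and therapy sessions as observed.
- Report the imputed result beside the complete-case economic result.
- Give the number followed only by the reduced request in each arm. The article already requires a file note for non-responders whose data were obtained this way.

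This needs no new data, only analysis wording and one extra set of results. If the unseen analysis plan already does it, only the counts by arm need adding.
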